### Relevant concomitant care permitted or prohibited during the trial {11d}

The protocol does not restrict participant access to usual care services. The usual care delivered at each site is documented at the point of site inclusion in the trial, at 12 months after the site opening and at 12 months after the last participant at the site is recruited. Participants also self-report their usual care received at 3-, 6- and 12-month post-randomisation. Should the trial team become aware of any new referrals to services, the nature of the referral will be established and discontinuation in the SLI considered.

### Provisions for post-trial care {30}

Should participants disclose anything to the trial team which puts them or anyone else at risk, the trial team may feel it necessary to report this to the appropriate persons. Additional exercise support outside of the SLI is not provided by CESs, and no specific aftercare is planned as part of the trial.

The NHS Sponsor is a member of the Clinical Negligence Scheme for Trusts (CNST) which provides indemnity cover for clinical negligent harm only. The Sponsor has an agreement in place with NH and therefore CNST indemnity extends to cover this service provider and their staff who have a duty of care to research participants.

### Outcomes {12}

Outcome data will be collected via participant self-report postal/online questionnaires and follow-up assessments with a local research nurse, or delegate, at 3-, 6- and 12-month post-randomisation. Supported completion of questionnaires by site staff can be requested by participants. If supported follow-up is required, wherever possible a research nurse, or delegate, who is blind to the participant’s allocation will offer telephone follow-up to participants who are unable to complete assessments independently. If site staff are subsequently unblinded, additional and subsequent data collection will be completed by an alternative researcher who is blinded to allocation.

#### Primary outcomes

Disease-specific QoL and fatigue at 12-month post-randomisation were measured by FACT-P [26] and FACIT-F [27]. The FACT-P [26] incorporates primary QOL domains: Physical Well-Being, Social/Family Well-Being, Emotional Well-Being, and Functional Well-Being with the addition of a prostate cancer-specific subscale. The FACIT-F [27] assesses perceptions of fatigue over the last 7 days.

#### Secondary outcomes

Secondary endpoints will be measured at 3-, 6- and 12-month post-randomisation and are as follows:

##### Questionnaire outcomes

Physical, Social/Family, Emotional and Function wellbeing, assessed using FACT-P [26] subdomainsCancer-specific fatigue (FACIT-F [27].)Leisure time physical activity assessed using the Godin [28] questionnaire.Fear of recurrence and psychological distress markers assessed using FCR4 [29] and FCR7 [29].Adverse effects of ADT assessed using trial specific ADT Symptom Index.Perceptions of capabilities, opportunities and motivations to perform a target behaviour assessed by the COM-B [30] Questionnaire.

##### Physical measures

Functional capacity and body composition assessed by blood pressure, chair sit-to-stand, waist and hip circumference and weight.

##### Safety

Adverse events assessed by:Number and proportion of RUSAEsNumber of RUSAEs per participantDetails of RUSAEs including severityNumber and proportion of deathsDetails of deaths including primary cause and timing

##### Health economics

Generic quality of life assessed using EQ-5D-5L [31] questionnaireCosts of the intervention and of health care resource useCost per incremental QALY using EQ-5D-5L [31] questionnairePatient preferences and willingness to pay for exercise programmes as assessed by the DCE [32].

##### Moderator/mediators

Moderator and mediator variables which influence engagement with and benefit from the intervention will also be measured.

### Participant timeline {13}

The trial timeline for participants is presented in Fig. 1, outlining the schedule of enrolment and interventions, and in Fig. 2, outlining the schedule of assessments.

**Fig. 1 Fig1:**
[figure not shown]
Schedule of enrolment and interventions

**Fig. 2 Fig2:**
[figure not shown]
Schedule of assessments

### Sample size {14}

A total sample size of 697 men (313 OUC, 384 SLI) is required to provide 90% power to detect a small to moderate effect size of either 0.33 in FACT-P [26] (8 point difference) or 0.35 in FACIT-F [27] (3 point difference) at the 5% significance level. Calculations assume a maximum standard deviation of 24 (FACT-P [26]) and 8.6 (FACIT-F [27]) and 30% loss to follow-up by 12 months [38]. Clustering at the level of the CES in the intervention arm is accounted for using an intracluster correlation coefficient (ICC) of 0.05 [39], a coefficient of variation of 0.6 to account for variation in the number of men each CES will deliver the intervention to, an average cluster size of 6 participants (range 1 to 14) per CES and 64 CES.

The sample size calculation takes into account the correlation between the two primary endpoints based on methodology by Micheaux et al. [40]. A correlation between FACT-P [26] and FACIT-F [27] of 0.7 (95% confidence internal (CI): 0.58–0.78) was observed at baseline in the pilot data [16]. The lower bound of the CI for the correlation estimate (0.58) was incorporated into the calculations. After accounting for multiple testing with correlated continuous multiple primary endpoints, the adjusted alpha level is 0.02768.

### Recruitment {15}

To ensure recruitment of 697 men within an 18-month period, the internal pilot green progression criteria for recruitment was set as at least 4 men per site per month from a minimum of 12 NHS Trusts based on a minimum of 40 men from each site, per year, over a total recruitment period of 18 months. Additional sites will be added during the recruitment period to deliver the overall sample size of 697 if required.

## Assignment of interventions: allocation

### Sequence generation {16a}

Participants will be randomised on a 5:4 basis to receive either SLI or OUC. A computer-generated minimisation programme incorporating a random element will be used to ensure arms are well-balanced for the following stratification factors:Age: < 70 years OR ≥ 70 yearsDuration on ADT: ≤ 12 weeks OR > 12 weeksReceiving chemotherapy and/or novel androgen receptor inhibitors: yes OR noReceiving radiotherapy: yes OR no

### Concealment mechanism {16b}

Randomisation will be performed using the Leeds CTRU automated 24-h randomisation service, which can be accessed via the web and ensures allocation concealment. Personal usernames and passwords required to access the randomisation system will be provided to sites when all relevant trial approvals are in place.

### Implementation {16c}

Following participant consent, confirmation of eligibility and collection of baseline data, a member of the SHU research team will randomise the participant. The principal investigator and relevant local research team at the site will receive an automated email confirmation of successful randomisation, highlighting subsequent tasks required and omitting randomisation allocation details. Participants will be contacted via letter/email to confirm their randomisation allocation. The research team at SHU will refer participants randomised to SLI to NH to initiate the exercise programme.

## Assignment of interventions: blinding

### Who will be blinded {17a}

Participants and NH staff will be aware of treatment allocation, but researchers involved in data collection, general practitioners (GP) and clinical teams will be blind to the allocation. Analysis will be conducted unblind to allocation according to pre-specified analysis plans.

It is not possible to blind participants or those involved in the delivery of the intervention in studies evaluating exercise/lifestyle interventions.

CTRU will regularly monitor for bias by reviewing participant characteristics (e.g. stratification factors, number of comorbidities and other characteristics as deemed appropriate) by the treatment arm to check for imbalances. CTRU and the trial management group (TMG) will monitor instances of unblinding to review for systematic errors that could impact upon trial integrity and elevate concerns to the programme steering committee (PSC).

### Procedure for unblinding if needed {17b}

Trial participation will be recorded in participants’ hospital notes and with their GP. This will not reveal allocation but will detail where further information can be gained if required. A central list of participants’ randomisation allocations will be maintained at SHU and at CTRU. We do not foresee a situation where allocation needs to be revealed outside of regular office hours.

## Data collection and management

### Plans for assessment and collection of outcomes {18a}

The schedule for participant assessments is summarised in Fig. 2: Schedule of assessments.

Baseline data for consenting patients will be collected by the research team at SHU from the participant directly. The local researcher at the participating site will collect data from medical records (e.g. blood pressure). Participants will self-complete all remaining assessments. Where inclusion in the trial is deferred until after completion of a course of chemotherapy, baseline assessments will be repeated before randomisation.

At 3-, 6- and 12-month post-randomisation, follow-up questionnaires will be completed by participants online or by post. Supported follow-up by site staff can be requested by participants. If questionnaires are not returned on time, up to three reminders may be sent via post, email, or text depending on the participants’ preferred method of contact. Where relevant, local researchers at participating sites will be asked by CTRU to confirm survival status and current address.

At 3-, 6- and 12-month post-randomisation, local researchers at participating sites will collect data from participants directly and from their medical records (e.g. blood pressure, changes in prostate cancer treatment). Any RUSAEs will also be collected.

Local researchers at participating sites will receive training on the completion of all trial-specific assessments as part of trial initiation, to ensure standardised completion. CTRU will chase missing and discrepant data as appropriate. Data collection forms are available on request at [contact].

### Plans to promote participant retention and complete follow-up {18b}

Initial/reminder letters, texts and emails will be used to maximise questionnaire data return at all timepoints. Participants may request support in the completion of questionnaires by site staff or the trial team in advance or during routine telephone reminders. The TMG will monitor questionnaire return rates overall and by the treatment arm.

A postcard from the PPI group will be sent to participants at 11 months to remind them their 12-month questionnaire will arrive soon and to encourage engagement with the project. A poster from the PPI group will also be sent to participants alongside their 12-month questionnaire to provide thanks, encouragement to complete the final questionnaire, and to remind participants how to receive the study results.

Participants will remain free to withdraw at any time from the trial without giving reasons and without prejudicing their further treatment. If a participant withdraws consent to participate, clarification will be sought on whether withdrawal is because of participation in the intervention, questionnaire completion or ongoing access to health records and data processing. Data collected up to the point of withdrawal will be included in the final trial analysis. This will be made clear to the participants at the time of consent and when they withdraw from the trial.

### Data management {19}

All data collection forms transferred to or from the CTRU will be coded with the participant’s trial number, initials and site code. Data will be held securely on paper and electronically at CTRU, Sheffield Hallam University and at NH. All relevant Standard Operating Procedures, Guidelines and Work Instructions in relation to data management, processing and analysis of data will be followed. CTRU will provide sites with an electronic file to safely maintain essential trial documentation. Interviews for the process evaluation will be audio recorded and professionally transcribed, with any identifiable information removed. Audio files will be securely transferred in encrypted format and securely stored at Queen Mary University London, Sheffield Hallam University and Bristol.

### Confidentiality {27}

All information collected during the trial will be kept strictly confidential, complying with all aspects of the 2018 Data Protection Act [41]. Appropriate storage, restricted access and disposal arrangements of personal and clinical details of participants will be put in place. At the end of the trial, sites will archive all trial data until written permission for confidential destruction is provided by the Sponsor. The Trial Master File and documents held by the CTRU will be archived at a secure facility at the University of Leeds.

### Plans for collection, laboratory evaluation and storage of biological specimens for genetic or molecular analysis in this trial/future use {33}

Not applicable; no samples were collected.

## Statistical methods

### Statistical methods for primary and secondary outcomes {20a}

A detailed Statistical Analysis Plan will be written before any analyses are undertaken. Final analysis will be conducted once all available outcome data is received. All analyses will be conducted on the intention-to-treat (ITT) population, with all participants included in the analysis according to their randomisation allocation, and regardless of non-adherence to the intervention or withdrawal from the trial. Blinded interim reports will be presented to the PSC containing descriptive summaries of recruitment, follow-up, safety and data quality.

#### Primary endpoint analysis

Primary analysis will compare mean FACT-P [26] and FACIT-F [27] scores at 12-month post-randomisation between the trial arms using partially nested mixed-effects linear regression models to account for clustering of outcomes in the intervention arm due to the nesting of participants within CESs [42]. The models will be adjusted for the stratification factors and other participant-level covariates expected a priori to be associated with the outcome of interest. Each endpoint will be tested against the calculated adjusted alpha level 0.02768. If a statistically significant result is observed in either FACT-P [26] or FACIT-F [27], the SLI will be deemed clinically different to OUC. Results will be expressed as estimated mean differences with 97.232% confidence intervals, *p*-values and ICCs. Model diagnostics will be visually assessed to check the underlying assumptions of the model and alternative methodology will be used if required.

#### Secondary endpoint analysis

Summary statistics will be presented for each time point by arm for secondary outcomes FACT-P [26] (overall and domain-specific), FACIT-F [27], leisure time physical activity (Godin [28]), fear of recurrence (FCR4 [29] and FCR7 [29]), adverse effects of ADT (ADT Symptom Index), functional capacity and body composition (blood pressure, chair sit-to-stand, waist and hip circumference and weight). Means, standard deviations, medians, minimum, maximum, quartiles and ranges will be presented for continuous variables and frequencies and percentages for categorical variables. Secondary endpoints will be analysed using the same approach as for the primary outcome with the relevant model for the type of outcome variable. Safety endpoints will be analysed descriptively between arms and no formal statistical comparisons will be made.

Moderators and mediators will be identified. Whether the treatment effect differs depending on the pre-specified baseline characteristics of the participant will be explored.

#### Internal pilot

Descriptive analysis of the internal pilot against progression criteria (Table 1) together with an examination of the sample size assumptions will take place after 12 months of recruitment.

**Table 1 Tab1:**
[figure not shown]
Progression criteria

^1^Data from August 2022 onwards will be used for analysis of this criterion to allow for a sufficient number of sites to be open and to ensure the trial has reached a steady rate of recruitment

^2^This target is set at a gym level. Therefore, for sites with 2 gyms, the criteria are green ≥ 8, amber < 8 and ≥ 4, and red < 4

^3^Based on 12 recruiting sites

^4^FACT-P [26] and FACIT-F [27] only

### Interim analyses {21b}

No formal interim analyses of outcomes will be undertaken.

### Methods for additional analyses (e.g. subgroup analyses) {20b}

No sub-group analyses are planned.

### Methods in analysis to handle protocol non-adherence and any statistical methods to handle missing data {20c}

We will explore missing data patterns and reasons for missingness to guide the assumptions around missing data. If it can be assumed that data is missing at random (MAR), the primary ITT analysis will use multiple imputation, enabling inclusion of all randomised participants. If data cannot be assumed MAR we will explore other more complex methods for the primary analysis such as pattern mixture modelling.

### Plans to give access to the full protocol, participant-level data and statistical code {31c}

Anonymised data supporting this work are available on reasonable request. All requests will be reviewed by relevant stakeholders, based on the principles of a controlled access approach. Requests to access data should be made to [contact] in the first instance.

## Economic evaluation

The economic evaluation will use data at 12 months and will adopt the NICE reference case employing a primary endpoint of cost per incremental QALY [43]. The primary perspective will be the health and personal social service provider, but will include supplementary analyses incorporating patient/caregiver costs (e.g. out-of-pocket expenses in attending exercise sessions).

Costs will include the costs of the interventions, costs of any additional exercise equipment and exercise facility access purchased or provided and any additional healthcare resources used (including primary and secondary care). Unit costs will be taken from the Personal Social Services Research Unit report and NHS Reference costs. Health outcomes will be assessed by the EQ-5D-5L [31] at follow-up but we will also explore basing utility on the FACT-P [26] and/or FACIT-F [27] measures (via mapping) depending on the availability of suitable mapping algorithms or direct valuation tariffs.

A Health economic analysis plan (HEAP) will be developed prior to analysis. The HEAP will be reviewed by the project team and an external health economist. The primary analysis will adopt an ITT approach but with additional pre-specified analyses conducted to evaluate the impact of intervention compliance on cost-effectiveness.

We will generate ICERs per QALY at 3, 6 and 12 months. We will use seemingly unrelated regression to account for the correlation between costs and QALYs and within this use relevant covariates to adjust for any imbalance across arms. We will use robust standard errors to account for any potential clustering in outcomes by CES in the intervention arm. The analytical process will also incorporate the strategy for handling missing data (e.g. multiple imputation, if appropriate) and the variance–covariance matrix used to generate 10,000 ICERs. The latter simulations will be plotted on the cost-effectiveness plane and help generate the cost-effectiveness acceptability curve to characterise the level of sampling uncertainty in the analysis.

A decision-analytic model will be developed to extrapolate costs and benefits over a lifetime horizon following consultation with clinical experts and patients. It will likely be a Markov Model. We will use trial data and targeted literature reviews to derive the model parameters and explore using resources such as the National Prostate Cancer Audit. We will generate lifetime ICERs for SLI vs. OUC. We will assume a cost-effectiveness threshold of £20,000 per QALY gained. We will generate net monetary benefit (NMB) and conduct extensive one-way and scenario deterministic sensitivity analyses. We will explore, the impact of different intervention costs, engagement and effectiveness decay over time on the estimates of cost-effectiveness. A probabilistic sensitivity analysis will capture the total parameter uncertainty in the model. Results from this will be presented in the form of cost-effectiveness planes, NMB distributions and cost-effectiveness acceptability frontiers [44].

We will use information from the discrete choice experiment on men’s willingness to pay and likely uptake for extended (and alternative) programmes to explore alternative funding strategies. These will be incorporated in supplementary analysis exploring the cost-effectiveness of alternative programmes.

## Process evaluation

The mixed methods process evaluation will be undertaken based on the Medical Research Council (MRC) guidance [45] for process evaluations and informed by the framework of Linnan and Steckler [46]. Quantitative and qualitative data will be collected to address five objectives. Data will be collected throughout the whole trial period to explore different stages of the intervention/trial. Further detail will be presented in a separate process evaluation protocol manuscript (*in preparation*).

## Oversight and monitoring

### Composition of the coordinating centre and trial steering committee {5d}

The coordinating centre (SHU) is responsible for intervention training and undertaking individual participant research activities, including consent, eligibility and data collection. The CTRU at the University of Leeds is responsible for set up, implementation and monitoring of trial conduct; data management and statistical design, analysis and reporting and is where the trial and data management and statistics teams are based.

The PSC will provide overall supervision of the trial and are responsible for monitoring trial progress and providing public, clinical, and professional advice. It will include an Independent Chair, at least two other independent members, and a PPI representative. The Committee will meet annually as a minimum.

The programme management group (PMG) oversees the STAMINA Programme Grant and includes the chief investigator, co-applicants and co-investigators. The PMG will oversee the whole programme of studies and meet twice annually as a minimum.

The TMG includes the chief investigator, trial and process evaluation leads, key co-applicants, the CTRU delivery team, the SHU research team, a PPI representative and other key external members of staff involved in the trial. The TMG will oversee trial set-up; on-going management; promotion of the trial; and the interpretation and publishing of the results. The TMG will meet quarterly as a minimum.

### Composition of the data monitoring committee, its role and reporting structure {21a}

For a trial of this nature, a separate Data Monitoring and Ethics Committee is not required. Rather, the PSC will adopt a safety function, with the constitution of a sub-committee to review safety issues, where necessary.

Summary safety data will be provided to the PSC to determine patterns and trends of events or to identify safety issues, which would not be apparent on an individual case basis.

### Adverse event reporting and harms {22}

Adverse events fulfilling the definition of related and unexpected are reportable in this trial (resulting from the administration of any of the research procedures). All related and unexpected serious adverse events will be reviewed by the principal investigator and reported to CTRU within 24 h of becoming aware. They will be subject to expedited reporting to the Sponsor and the Research Ethics Committee (REC) within 15 days. Where the principal investigator is unable to decide whether or not the serious adverse event is either ‘related’ or ‘unexpected’, the event should be reported to the chief investigator, who will liaise with the coordinating centre and CTRU in arriving at a decision. Events will be followed up until the event has been resolved or a final outcome has been reached.

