#### Secondary objectives

To establish whether the intervention promotes physical, social, emotional, and functional wellbeing at 3-, 6- and 12-month post-randomisation using FACT-P [26] subdomains.To establish whether the intervention reduces cancer-specific fatigue at 3- and 6-month post-randomisation using FACIT-F [27].To establish whether the intervention increases leisure time physical activity, measured using the Godin [28] questionnaire at 3-, 6-, and 12-month post-randomisation.To establish whether the intervention reduces fear of cancer recurrence measured using Fear of Cancer Recurrence (FCR4 and FCR7) [29] at 3-, 6- and 12-month post-randomisation.To establish whether the intervention improves functional capacity and body composition, measured using blood pressure, chair sit-to-stand, waist and hip circumference and weight at 3-, 6-, and 12-month post-randomisation.To establish related and unexpected serious adverse event (RUSAE) rates, and severity.To establish whether the SLI reduces adverse effects, commonly associated with ADT measured using a trial-specific ADT symptom index at 3-, 6- and 12-month post-randomisation.To establish participants’ perceptions of capabilities, opportunities, and motivations to perform a target behaviour using the Capability, Opportunity, Motivation-Behaviour (COM-B) [30] Questionnaire.To establish whether the intervention is cost-effective, assessed using incremental cost-effectiveness ratios (ICERs). The outcome of interest is cost per incremental quality-adjusted life year (QALY) at 12-month post-randomisation with QALYs being derived from the EuroQol 5 Domains 5 Levels (EQ-5D-5L) [31].To establish patient preferences and to predict demand for alternative extended exercise programme features using a discrete choice experiment (DCE) [32].To establish moderator and mediator variables which influence engagement with and benefit from treatment.

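### Apart from deaths, the safety outcomes count only serious events judged both related and unexpected, so the by-arm table cannot show whether serious morbidity differs between arms

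*Protocol article*

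**What the plan says.** All references are to the protocol article.

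- **Secondary objectives.** The safety objective is "To establish related and unexpected serious adverse event (RUSAE) rates, and severity".
- **Outcomes {12}, Safety.** Two kinds of outcome are listed: RUSAEs (number, proportion, number per man, details with severity) and deaths (number, proportion, cause, timing). Deaths carry no condition on relatedness or expectedness.
- **Plans for assessment and collection of outcomes {18a}.** For the 3-, 6- and 12-month data collection by local researchers: "Any RUSAEs will also be collected". No other adverse event collection is named.
- **Adverse event reporting and harms {22}.** The filter is set at the start of this section: "Adverse events fulfilling the definition of related and unexpected are reportable in this trial". A parenthesis there ties it to events caused by a research procedure. The next sentence adds seriousness: "All related and unexpected serious adverse events will be reviewed by the principal investigator and reported to CTRU within 24 h of becoming aware".
- **Secondary endpoint analysis.** "Safety endpoints will be analysed descriptively between arms and no formal statistical comparisons will be made".
- **Data monitoring committee {21a}.** There is no separate committee; the programme steering committee (PSC) takes on the safety function. "Summary safety data will be provided to the PSC to determine patterns and trends of events or to identify safety issues".
- **Implementation {16c} and Who will be blinded {17a}.** The randomisation email to the principal investigator leaves out the allocation, and clinical teams are to be blind to it.
- **Outcomes {12}, Health economics, and Economic evaluation.** Health care resource use is an outcome, and costs cover "any additional healthcare resources used (including primary and secondary care").

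**The concern.** A filter suited to expedited reporting also defines the safety outcome. An event enters the count only if it is serious, attributed to a research procedure and classed as unexpected. Two problems follow for a table laid out by arm.

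First, the scope for attribution is unequal. SLI men have a 12-month exercise programme to which an event could be related. Men on optimised usual care (OUC) have advice, a telephone safety check, an information pack and the assessments common to both arms. A difference in RUSAEs then mixes any difference in harm with the difference in what there is to attribute an event to.

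Second, the filter removes events that bear on net harm or benefit. A related serious event classed as expected is not counted, and neither is any serious event judged unrelated. An excess or a reduction in overall serious morbidity would therefore not show, unless it led to death.

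At stake is what the trial can say about harm when its results are used to inform NHS implementation, and what the PSC has in front of it when it looks for patterns.

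**Working it through.** **Step 1: is the restriction confined to expedited reporting?** No. The objective, the outcome list, the follow-up data collection and section {22} all use the same category. The one unfiltered component is death. The ADT Symptom Index measures effects of androgen deprivation and does not fill the gap for exercise-related harm.

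**Step 2: is attribution symmetric?** Intervention description {11a} gives OUC to both arms and the exercise programme to SLI only. Both arms undergo some research procedures, including the chair sit-to-stand test, so control attribution is possible but has less scope. The principal investigator reviews events, yet {16c} and {17a} intend the local team not to know the allocation. Either relatedness to exercise is judged without knowing whether the man was allocated exercise, or the event itself reveals the arm. The first risks misclassification; the second lets the judgement depend on arm.

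**Step 3: what could the RUSAE count show?** The article states no safety event rate and no safety sample size, so there is no planned safety figure to reproduce. The arm sizes (313 OUC, 384 SLI) come from Sample size {14}. The 90% efficacy power there does reproduce. With 30% loss and a mean cluster of 6 × 0.7 = 4.2, the design effect is 1 + ((0.6² + 1) × 4.2 − 1) × 0.05 = 1.236, and FACT-P power is 0.900 at alpha 0.02768. The safety point does not depend on it.

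Upper 95% limits with zero events among n men:

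- One-sided, 1 − 0.05^(1/n): n = 384 gives 0.78%.
- Two-sided, 1 − 0.025^(1/n): n = 384 gives 0.96%; n = 313 gives 1.17%.

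For **assumed** SLI RUSAE risks, with no control events:

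| Assumed SLI risk p | Expected events, 384p | Chance of none, (1 − p)^384 | Power of Fisher's test, two-sided 5% |
|---|---|---|---|
| 0.2% | 0.8 | 46% | about 0% |
| 0.5% | 1.9 | 15% | 1% |
| 1% | 3.8 | 2% | 19% |
| 2% | 7.7 | <0.1% | 78% |

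Six events against none would be needed for p < 0.05 (6 v 0: p = 0.035; 5 v 0: p = 0.068). No test is planned; this only shows how little a sparse table carries.

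**Step 4: what would an allocation-neutral count add?** With **assumed** admission risks of 15% (OUC) and 20% (SLI), 0.15 × 313 = 47 and 0.20 × 384 = 77 men are affected. If the planned 30% loss applied to this outcome, the denominators fall to 0.7 × 313 = 219 and 0.7 × 384 = 269, giving about 33 and 54 men. At full numbers a formal two-proportion test would have about 40% power for 15% v 20%, 50% for 10% v 15%, 86% for 20% v 30% and 91% for 15% v 25%. The added table would be descriptive and would not settle a modest difference, but it would count the same thing in both arms.

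**The case against.** The other side has real points.

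- *Deaths.* A reader might infer that safety rests on RUSAEs alone. It does not: deaths are listed for both arms without any filter and can be set side by side.
- *Control events.* A reader might infer that the control count is near zero by construction. The article gives no control rate, and OUC men also have a safety check, exercise endorsement, behavioural support where appropriate, and a sit-to-stand test. Less scope for attribution is a fair inference; near zero is not stated.
- *Conclusions from the count.* A reader might infer that the trial will declare the programme safe from a low RUSAE count. No section says so. The analysis is descriptive and formal comparison is ruled out.
- *Expected events.* A reader might treat the exclusion criteria as showing which harms would be dropped as expected. They say who may not enter. The definition of unexpected is not reproduced in the article, and the full protocol is not shown, so which exercise-related events would be dropped is unknown.
- *Proportionality.* Section {11b} calls the risks minimal and cites a systematic review of trials with no increase in serious adverse events. Limited collection is a defensible choice in that light, and overall service use is captured as a cost.

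These points limit the finding without removing it. Whatever the full definition of unexpected, it can only take related events out of the count. A table without a test still invites reading across its columns. Capturing service use as a cost does not by itself put admissions in front of a reader as a safety outcome.

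**Conclusion.** The point holds in a limited form. Apart from deaths, the safety outcomes cover only serious events judged both related to research procedures and unexpected. Attribution is likely to differ by arm, so the by-arm RUSAE table cannot show whether serious morbidity differs. The defect is an asymmetric and sparse description; it is not a failed test or a wrong figure, and the efficacy analysis is untouched.

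Its size cannot be computed from the article. The zero-event limit of 0.78% (one-sided; 0.96% two-sided) applies to the RUSAE category only and says nothing about all serious events. The RUSAE and admission risks used above are assumptions for illustration. The conclusion rests on the outcome and collection sections being complete as to what is counted; the full protocol may define relatedness and expectedness further.

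**What to change.** Leave RUSAEs, deaths and expedited reporting as they are, and make two additions.

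1. In Outcomes {12}, Safety, add a descriptive, allocation-neutral outcome: *number and proportion of men with any hospital admission or emergency attendance by 12 months, by arm, regardless of relatedness or expectedness*. Derive it from the secondary-care resource-use data and the record review at 3, 6 and 12 months. First confirm that those forms itemise admissions and emergency attendances, because the article does not say that they do.
2. In Secondary endpoint analysis, add: *RUSAE counts are listed by arm and are not read as a comparison of harm.*

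The cost is one descriptive table and two sentences if the items are already on the forms. If they are not, a form change is needed and would reach only assessments still to come; the second addition can be made regardless.

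The table has limits that should be stated with it. Resource use may be partly self-reported by unblinded men, the planned 30% loss to follow-up may apply, and reasons for admission may be incomplete. Give the number of men with data in each arm as the denominator.
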